### Endpoints

The endpoints pertain to the individual level. Patient discomfort will be assessed using the French self-reported discomfort IPREA questionnaire ("Inconforts des Patients de REAnimation": Discomforts perceived by ICU patients) [22]. IPREA is a well-validated specific questionnaire that is elaborated using standard procedures. This self-reported questionnaire includes 16 discomfort items: noise; excess of light; discomfort related to sleeping in a bed different from the one the patient has at home; sleep deprivation; thirst; hunger; feeling of cold; feeling of heat; pain; being tied down by perfusion lines, tubes, or as a result of connections due to monitoring devices; no respect for intimacy; anxiety; isolation; limited visiting hours; absence of phone; and lack of information. Each item is scored from 0 (minimal discomfort) to 10 (maximal discomfort). The overall discomfort score is calculated as the mean of all the scores reported for each discomfort item multiplied by 10, yielding an overall discomfort score between 0 (minimal overall discomfort) and 100 (maximal overall discomfort). The questionnaire is administered on the day of ICU discharge. The time frame considers the period from the date of admission to the ICU until the day of discharge from the ICU.

### Primary endpoint

The primary endpoint is the monthly overall discomfort score of the 16-item IPREA (mean of all the overall discomfort scores available during the month).

#### Secondary endpoints

The secondary endpoints are the monthly discomfort scores of the 16 items included in IPREA.

### Statistical considerations

#### Sample size, power, and statistical methods

The sample size was determined to detect a 25 % difference in the overall score of IPREA between the two groups. This 25 % difference, considered to be clinically significant, was based on a previous report indicating a mean overall discomfort IPREA score of 22 (standard deviation of 14). The intracluster correlation coefficient (ICC) was estimated from the database of the IPREA questionnaire validation study. With a design effect calculated to be 2.9 (ICC = 0.1; expected equal cluster sizes = 20), a two-sided significance level of 5 %, and 80 % power, 630 IPREA scores are needed (315 in each group) to detect this difference. To prevent 10 % of the questionnaires being unusable or invalid, a total of 700 individuals should be included.

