**Methods/design:**

We conducted a multicenter, cluster-randomized, controlled, single (patient)-blind study involving 34 French adult ICUs. The experimental intervention was a 6-month period during which the multicomponent program was implemented in the ICU and included the following steps: identification of discomforts, immediate feedback to the healthcare team, and implementation of targeted interventions. The control intervention was a 6-month period during which any program was implemented. The primary endpoint was the monthly overall score of self-reported discomfort from the French questionnaire on discomforts in ICU patients (IPREA). The secondary endpoints were the scores of the discomfort items of IPREA. The sample size was 660 individuals to obtain 80 % power to detect a 25 % difference in the overall discomfort score of IPREA between the two groups (design effect: 2.9).

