#### Randomization of clusters

Active consultation is conducted by the coordinating investigator among ICU heads in each potential participating ICU to ensure agreement regarding implementation of the program on the ICU level. Computer-generated randomized lists will be drawn up before the beginning of the study using a permuted block design, for which the clinical research unit (AP-HM) will be responsible. The randomization will be stratified by the average monthly number of patients not deceased during ICU discharge during the year preceding the start of the study (three levels were considered: ≤35, 36–59, and ≥60). The randomization will assign each ICU (1:1 allocation ratio) to either control or experiment. The investigators and caregivers will not be blinded, but all participants will be unaware of the ICU allocation.

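### The abstract's 660 individuals and the methods' 630 scores/700 individuals cannot both be the sample size, and the design effect of 2.9 assumes equal clusters of 20, which is implausible

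*Protocol article*

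**What the plan says.** The sample size appears in two places in the protocol article.

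- **Abstract, Methods/design:** "The sample size was 660 individuals to obtain" 80 % power for a 25 % difference in the overall IPREA score, with a design effect of 2.9.
- **Sample size, power, and statistical methods:** this section opens with the aim, namely that "The sample size was determined to detect a 25 % difference in the overall score of IPREA between the two groups". The inputs are "a mean overall discomfort IPREA score of 22 (standard deviation of 14") and, for clustering, a "design effect calculated to be 2.9 (ICC = 0.1; expected equal cluster sizes = 20"). The error rates are set at "a two-sided significance level of 5 %, and 80 % power". The result is that "630 IPREA scores are needed (315 in each group) to detect this difference". After allowing for 10 % unusable questionnaires, "a total of 700 individuals should be included".

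Three other sections bear on the cluster size and on the comparison being sized.

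- **Randomization of clusters:** "The randomization will be stratified by the average monthly number of patients not deceased during ICU discharge", with levels of ≤35, 36–59 and ≥60.
- **Design:** there are 34 ICUs, 17 per group. In each one-month assessment period (P1, P3, P5) all eligible patients may enter, and no limit per ICU is stated.
- **Data analysis:** the primary comparison is B versus E, one month of data in each group, which is P3.

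**The concern.** Power, difference and design effect are the same in both places, so the sample size should be the same too. It is 660 in one and 630 evaluable/700 included in the other, and a reader cannot tell which target governed recruitment or which one the final report should be held to. The methods section does not name its formula, so the conflict cannot be settled from the text alone.

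The second issue is the factor of 2.9. It is exact only if every ICU contributes the same number of scores. Where ICUs differ in volume and all eligible patients of a month may enter, cluster sizes will vary. For a comparison that weights patients equally, that variation raises the true design effect, and the 80 % claim depends on it.

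**Working it through.** **Inputs, all from the sample-size section:** mean 22, so 25 % is 5.5 points; SD 14; two-sided 5 % (z = 1.960); 80 % power (z = 0.842); ICC 0.1; cluster size m = 20; 10 % unusable.

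**Step 1. Design effect.** 1 + (20 − 1) × 0.1 = 2.9. Reproduced.

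**Step 2. Methods total, 630/700.**
- Per arm without clustering: 2 × (14 × 2.802 / 5.5)² = 101.71.
- With clustering: 101.71 × 2.9 = 294.96 per arm, or 294.96 / 20 = 14.75 clusters.
- One cluster added per arm, a standard small-sample correction in cluster trials: 15.748 × 20 = 314.96, so 315 per arm and 630 in total.
- Unusable questionnaires: 630 / 0.9 = 700.

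Both methods figures reproduce exactly. A t-based calculation comes to nearly the same place: about 630 scores with 30 degrees of freedom and about 628 with 32. The text does not say which route was taken.

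**Step 3. Abstract total, 660.**
- Simple formula, no added cluster: 2 × 294.96 = 590, and 590 / 0.9 = 656. Rounding 101.71 up to 102 first gives 592 and 658.
- Rounding 14.75 up to 15 whole clusters per arm gives 2 × 15 × 20 = 600, and 600 × 1.1 = 660.
- From the methods' own figure: 630 / 0.9 = 700 and 630 × 1.1 = 693. Neither is 660.

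The abstract's figure fits a calculation without the added cluster, and the methods' figure fits one with it.

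**Step 4. Power of 315 per arm on the simple formula.** Φ(5.5 / (14 × √(2 × 2.9 / 315)) − 1.96) = Φ(0.935) = 82.5 %.

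**Step 5. Unequal clusters.** The article gives no CV of cluster size, so the CVs below are assumptions. For a patient-weighted comparison the design effect is 1 + ((1 + CV²) × m − 1) × ICC. At CV 0.4, for example, it is 1 + (1.16 × 20 − 1) × 0.1 = 3.22.

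| Assumed CV | Design effect, m = 20 | Power, 315 per arm, patient-weighted, normal approximation | Power, 630 scores in 34 ICUs (m = 18.5), patient-weighted, t with 32 df | Same, mixed-model weights |
|---|---|---|---|---|
| 0 | 2.90 | 82.5 % | 82 % | 82 % |
| 0.3 | 3.08 | 80.2 % | 80 % | 81 % |
| 0.4 | 3.22 | 78.5 % | 78 % | 81 % |
| 0.6 | 3.62 | 73.6 % | 73–74 % | 79 % |

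The fourth column uses m = 630 / 34 = 18.5. The last column weights each ICU by n / (1 + (n − 1) × 0.1), with gamma-distributed sizes n.

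**The case against.** The best defence is that the methods section is internally sound. 630 and 700 follow exactly from its inputs with a standard correction, and an article may leave the name of that correction to the full protocol. On the simple formula the target is generous. Equal clusters are declared openly as a planning expectation, and a mixed model loses little if sizes vary. On this view only the abstract needs correcting. Most of this stands, and it rules out four stronger readings that a reader might infer.

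- **That 630/700 is a miscalculation, needing an SD near 14.5 or a difference near 5.3.** This follows only if the simple formula is the one used, and the text does not say that. The exact match with one added cluster per arm speaks against it.
- **That 700 covers all three assessment months, leaving the primary test with a third of its patients.** 700 over 34 ICUs and three months is 700 / 102, or about 7 per ICU-month. That does not fit 20 per cluster or 315 per group in a single-month comparison. The text could say P3 outright, but its numbers already point there.
- **That 34 × 20 = 680 is a third conflicting total.** The 20 sits inside the design effect and is most naturally the number of analysed scores per ICU; 680 scores would exceed 630.
- **That the strata rule out equal clusters.** They count all live discharges. Analysed patients must also have stayed at least 3 days, consented, and met the cognitive and language criteria. The strata make equal sizes of 20 unlikely, not impossible.

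The defence does not remove the conflict between 660 and 700, and it does not justify a CV of zero.

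**Conclusion.** The conflict is certain and needs no assumption: the abstract's 660 and the methods' 630/700 are different targets for one power claim, 40 individuals apart on inclusion (700 − 660). That they come from calculations without and with an added cluster is an inference from the arithmetic, though a close one. The methods figure is the better supported of the two, since it is given with its inputs and reproduces exactly.

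The cluster-size point is a matter of degree. On the normal approximation with m = 20, 630 scores hold 80 % power up to a CV of about 0.3. Beyond that, a patient-weighted comparison falls to about 78 % at 0.4 and 74 % at 0.6, while mixed-model weighting stays near 79–81 %. These figures rest on assumed CVs and on the stated ICC of 0.1. They do not show that the trial is seriously underpowered. They show that the 80 % is conditional on something the article treats as given.

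**What to change.** 1. Correct the abstract to 630 evaluable scores and 700 individuals included.
2. State in the methods that this target applies to the P3 comparison (B versus E).
3. Name the sample-size formula, including any cluster added per arm or any t-based correction.
4. Restate the design effect as 1 + ((1 + CV²) × m − 1) × ICC. Take the CV from the ICUs' monthly discharge volumes, which are already known because they define the strata, and note that they only approximate the spread in analysed patients. Quote the resulting power for the analysis that will be used.

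The cost is a text correction and a short recalculation. No extra patients and no design change are needed. The only downside is that the stated power may come out slightly less favourable.

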The primary endpoint (mean of the overall discomfort scores collected during the 1-month period, B versus E in Fig. 1) will be analyzed without adjustment by comparison of IPREA scores between the two groups using Student *t*-tests or Mann–Whitney tests according to the variable distribution. A set of secondary analyses will be adjusted for covariates of clinical interest using generalized linear mixed regression models including the group (interventional/control), ICUs and individuals (as random variables), a priori covariates (patient age, gender, ICU stay duration, mechanical ventilation duration, and type of admission), and other co-variables selected with a threshold *p*-value <0.05 during univariate analysis. These models will be performed using the MIXED SAS procedure (version 9.2). The same procedure will be performed on the 16 IPREA scores for each discomfort item (B versus E in Fig. 1).

Generalized linear mixed regression models will be performed to assess the sustainability of the effect by comparison of monthly means of overall discomfort scores collected during periods P3 and P5, respectively, reported by patients included in the experimental group at 6-month intervals (B versus C in Fig. 1) and the seasonality effect by comparison of monthly means of overall discomfort scores collected during periods P1 and P3, respectively, reported by patients included in the control group at 6-month intervals (D versus E in Fig. 1).

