### Data collection

The following ICU-specific parameters will be recorded: type of ICU (medical, surgical, or mixed medical–surgical); number of beds; mean of stay duration; annual mortality rate.

Data related to the patient will be recorded from an electronic case report form (eCRF) specifically elaborated for the study. The following data will be collected: demographics (sex, age); health status before the ICU stay using the Knaus score [34] and the McCabe index [35]; health status at ICU admission using the Simplified Acute Physiology Score (SAPS II) [36]; type of admission (medical, scheduled surgical, or emergency surgical); health status from the ICU admission to ICU discharge (use and duration in days of mechanical ventilation, noninvasive ventilation, administration of vasopressors, renal replacement therapy, type and number of invasive procedures, sedation duration, delay between interruption of the sedation and discharge from the ICU); and self-perceived discomforts (IPREA, see the Endpoints section) assessed on the day of ICU discharge during the specific periods of assessment.

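### The secondary adjusted models fix ICU stay and ventilation duration, both accrued under the program, as covariates, so they may not estimate the total program effect

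*Protocol article*

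**What the plan says.** All of this is in the protocol article.

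- **Primary comparison (Data analysis).** The overall IPREA score in period 3, B versus E, "will be analyzed without adjustment by comparison of IPREA scores between the two groups".
- **Adjusted models (Data analysis).** "A set of secondary analyses will be adjusted for covariates of clinical interest using generalized linear mixed regression models". The fixed and selected covariates are "a priori covariates (patient age, gender, ICU stay duration, mechanical ventilation duration, and type of admission), and other co-variables selected with a threshold" of p below 0.05 in univariate analysis. ICUs and individuals both enter as random terms. The same procedure is then applied to the 16 item scores.
- **When the variables arise (Data collection).** Ventilation belongs to the block described as "health status from the ICU admission to ICU discharge (use and duration in days of mechanical ventilation". That block also holds noninvasive ventilation, vasopressors, renal replacement therapy, invasive procedures, sedation duration and the delay from sedation stop to discharge.
- **Severity before exposure (Data collection).** The Knaus score and McCabe index describe health before the ICU stay, and SAPS II describes it at ICU admission. None of the three is in the fixed list.
- **Exposure (Design; Discussion).** When period 3 starts, the experimental ICUs have run the program for 5 months, and they continue it. The Discussion says it reaches every patient in the unit.
- **Reason for adjusting (Discussion).** Consecutive inclusion may produce selection bias, to be assessed and adjusted for if present.

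**The concern.** Adjustment in a cluster trial that includes patients after randomization should remove chance or selection differences in case mix. It does so safely only with variables the intervention cannot have changed. Stay and ventilation duration are complete only at discharge, after a stay spent wholly under program or usual care. If the program alters them, holding them constant takes out part of what the program did. If an unmeasured severity factor drives both duration and discomfort, it also introduces a spurious difference.

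The practical stake is interpretation. If adjusted and unadjusted results differ, a reader cannot tell whether case mix was corrected or program effect was removed. The selection rule adds to this: post-admission items could enter, SAPS II, Knaus and McCabe might not, and the 17 models (overall score plus 16 items) could each carry a different set of covariates chosen from the data.

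**Working it through.** The plan gives no figure on this point to reproduce. The only number needed is the target effect from the sample-size section: 25% of a mean of 22, so 0.25 × 22 = 5.5 points (a reduction, -5.5).

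**Step 1: timing.**

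| Variable | When fixed | Role in the plan |
|---|---|---|
| Age, sex, admission type | By admission | A priori covariate |
| Knaus, McCabe | Before the stay | Only if selected |
| SAPS II | At admission | Only if selected |
| Stay duration | At discharge | A priori covariate |
| Ventilation duration | Between admission and discharge | A priori covariate |
| Sedation, vasopressors, procedures | Between admission and discharge | No stated bar to selection |

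**Step 2: what adjustment does.** In a linear model with one added covariate,

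adjusted effect = total effect - a × b,

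where *a* is the difference in mean duration between groups (program minus control) and *b* is the within-group slope of the score on duration. If *a* comes from case mix, removing a × b is useful. If the program caused *a*, removing it moves the estimate away from the total effect. The model cannot separate the two. If the program has no effect on duration, nothing is lost.

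**Step 3: illustration under assumed inputs.** The documents give neither *a* nor *b*.

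*Mediation.* If a share s of the effect runs through duration, the adjusted model targets -5.5 × (1 - s):

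| s | Adjusted target |
|---|---|
| 0% | -5.50 |
| 10% | -4.95 |
| 20% | -4.40 |
| 30% | -3.85 |

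The upper rows are demanding. With stay shortened by 0.2 SD, a 30% share needs b = 0.30 × 5.5 / 0.2 = 8.25 points per SD of stay, more than half of the score's SD of 14. A 10% share needs 0.10 × 5.5 / 0.2 = 2.75.

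*Shared unmeasured severity, no mediation.* Let severity correlate 0.5 with stay and be worth 4 points per SD, so b = 0.5 × 4 = 2:

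- program shortens stay by 0.2 SD: -5.5 - (-0.2 × 2) = -5.1
- no effect on stay: -5.5
- program lengthens stay by 0.2 SD: -5.5 - (0.2 × 2) = -5.9

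The distortion can therefore go either way.

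**Step 4: simulation.** The setting was 34 clusters of 20, SD 14, ICC 0.1, total effect -5.5, stay shortened by 0.2 SD, 400 runs per setting, with least-squares point estimates. Adding stay duration moved the mean estimate from -5.67 to -5.10 (share 10%), -5.61 to -4.49 (20%) and -5.58 to -3.94 (30%). These are shifts of 0.57, 1.12 and 1.64, against 0.55, 1.10 and 1.65 from the formula. With no mediation and no shared severity, there was no shift (-5.50 in both models). With shared severity only, the estimate moved from -5.55 to -5.15, a shift of 0.40, as the formula gives.

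**The case against.** The strongest defence has four parts.

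1. **The primary analysis is unadjusted**, so the total effect is reported whatever these models show. This stands. A reader might infer that the trial's main result is biased; the documents do not support that.
2. **No passage says the program shortens stay or ventilation.** The Background links discomfort to agitation and delirium, not to duration. Bedside feedback comes on the day of discharge, too late to change that patient's own stay. Only the earlier unit-level actions could, and they differ between ICUs. This stands as a limit on size. A reader might infer a known loss, or one always toward zero; the documents support neither.
3. **The durations have a rationale.** IPREA asks about the whole stay, so stay length is the recall window, ventilation is itself a source of discomfort, and the Discussion notes large differences in patients between ICUs. This is fair, and it is a reason to keep a duration model as an exploratory analysis. It does not make the durations baseline variables, and measures that precede exposure are already collected.
4. **The candidate list for selection is not shown in a condensed article.** SAPS II, Knaus and McCabe are as eligible as sedation or vasopressors. This stands: they are not excluded, only not guaranteed. Nor does the p-value rule by itself remove any effect. The two durations, however, are named outright as fixed covariates.

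The individual random term may be loose wording for patient-level residual variation. Read literally, it is redundant with the residual when each patient gives one score, and it would not bias the program estimate.

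**Conclusion.** The point holds for the secondary adjusted models, covering the overall score and the 16 items. They fix two post-exposure durations as covariates and add an open-ended p-value selection. If the program affects either duration, the adjusted estimate does not target the total program effect and can be off in either direction.

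The size cannot be determined from the documents. The range above (no change at all, up to 1.65 of 5.5 points at an assumed 30% mediated share) shows the mechanism and is not an estimate. It rests on an assumed program effect on duration and an assumed slope. The conclusion that these covariates are post-exposure rests on the text alone.

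**What to change.** In the adjusted models:

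- Replace stay and ventilation duration with SAPS II, the Knaus score and the McCabe index, alongside age, sex and admission type.
- Add the randomization stratum (average monthly number of patients, three levels) and the ICU's period 1 mean discomfort score.
- Fix this list in advance for all 17 models and delete the univariate p<0.05 selection.
- Report any model with stay or ventilation duration only as a labelled exploratory analysis.
- Minor wording: keep only the ICU random effect.

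The patient covariates are already in the eCRF, the stratum is known at randomization, and period 1 scores are already planned. The two added ICU-level terms use 3 of the between-ICU degrees of freedom (2 for the stratum, 1 for the baseline mean), leaving 34 - 2 - 3 = 29. The downside is small: the main adjusted models no longer account for differences in the recall window, which then appear only in the exploratory model.

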### Objectives

The primary objective was to assess the effectiveness of the multicomponent program of discomfort reduction in the ICU. The secondary objectives were to assess sustainability and a potential seasonality effect of this program.

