## Methods/design

### Design

The study design was built to achieve both the primary and the secondary objectives. To achieve the primary objective, a multicenter, cluster-randomized, controlled, single (patient)-blind, two-parallel group study was designed using the recommendations of the Consolidated Standards of Reporting Trials (CONSORT extension for Cluster Trials) statement [33]. The cluster level comprises the ICUs, which are the units of randomization. Patients hospitalized in the ICUs comprise the individual level. All ICUs start with a 1-month period with no intervention, and then they are randomized to one of two groups: a 6-month period during which the multicomponent program (experimental group) is implemented or a 6-month period during which any program (control group) is implemented.

To assess the sustainability of the impact of the program, the study was completed with a second 6-month period during which the program was no longer applied in the ICUs randomized to the experimental group. During this second 6-month period, the program was applied in the ICUs randomized to the control group. We hypothesized that the multicomponent program of discomfort reduction is considered attractive for caregivers in the participating ICUs, leading to an initial preference for the investigators to be randomized to the experimental group. The inferred risk is better adherence to the study in the ICUs randomized to the experimental group in comparison with the other ICUs randomized to the control group and, therefore, an imbalance in the number of included patients in the two groups. That is the reason why the study was designed to offer the opportunity to all the ICUs to implement the program, no matter when the cluster randomization may occur (whether during the first 6-month period or during the second 6-month period).

Moreover, the prolongation of the study for a 6-month period (leading the ICUs that were initially randomized to the control group to test the program) allows assessment of the potential seasonality effect of the program (because the program will be applied during another part of the year) and the ability to obtain eventual confirmation of the impact of the program in other ICUs.

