Thus, five periods are differentiated and illustrated in Fig. 1. Period 1 lasts 1 month, during which none of the 34 ICUs apply the multicomponent program. All the eligible patients can be included and can be assessed using the self-perceived discomfort questionnaire, but no feedback of scores will be given to the healthcare teams. Thus, baseline discomfort levels will be available. Period 2 lasts 5 months, during which the 17 ICUs randomized to the experimental group will implement the multicomponent program as detailed below, whereas the 17 ICUs randomized to the control group will not implement it. Period 3 lasts 1 month, during which all the eligible patients of the 34 ICUs can be included and can be assessed using the self-perceived discomfort questionnaire. The 17 ICUs randomized to the experimental group will continue to apply the program with feedback information (last month of the 6-month period for implementation of the program), whereas the 17 ICUs randomized to the control group will receive no feedback. Period 4 lasts 5 months, during which the 17 ICUs initially randomized to the control group will implement the multicomponent program as detailed below, whereas the 17 ICUs initially randomized to the experimental group will no longer implement it. Period 5 lasts 1 month, during which all the eligible patients of the 34 ICUs can be included and can be assessed using the self-perceived discomfort questionnaire. The 17 ICUs randomized to the control group will continue to apply the program with feedback information (last month of the 6-month period for implementation of the program), whereas the 17 ICUs randomized to the experimental group will receive no feedback.

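### The planned seasonality analysis compares two usual-care months in control ICUs, so it cannot show whether the program's effect varies by season, which is the objective as worded

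*Protocol article*

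**What the plan says.** The Objectives section reads: "The secondary objectives were to assess sustainability and a potential seasonality effect of this program". The Design section explains how the design serves this aim: prolonging the study by six months "allows assessment of the potential seasonality effect of the program (because the program will be applied during another part of the year", and also gives "the ability to obtain eventual confirmation of the impact of the program in other ICUs".

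The Data analysis section assigns the aim to a specific contrast, "the seasonality effect by comparison of monthly means of overall discomfort scores collected during periods P1 and P3", "reported by patients included in the control group at 6-month intervals (D versus E in Fig. 1".

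The description of the five periods in the Design section fixes what the control ICUs are doing in each assessment month:

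- P1: "Period 1 lasts 1 month, during which none of the 34 ICUs apply the multicomponent program".
- P3: the experimental ICUs are in their last program month, "whereas the 17 ICUs randomized to the control group will receive no feedback".
- P5: "The 17 ICUs randomized to the control group will continue to apply the program with feedback information".

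The only other contrasts named are B versus E (the primary endpoint, repeated for the 16 items) and B versus C (sustainability, within the experimental group).

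**The concern.** The objective asks whether the program works differently at different times of year. The analysis assigned to it ends at P3, before the control ICUs have used the program at all. It also ends before the second program period, which the Design section gives as the reason the question can be answered.

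Followed as written, the trial would report a six-month change in discomfort under usual care as its seasonality effect. A reader going by the Objectives section would take that as a statement about the program. The scores that do bear on the program in another season, those of the control ICUs at P5, would be collected without being assigned to any contrast named in the article.

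**Working it through.** **Cells.** Figure 1 is not shown, but the text fixes B, C, D and E by arm and period. The labels A and F for the two remaining cells are inferred.

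| | P1 (month 1) | P3 (month 7) | P5 (month 13) |
|---|---|---|---|
| Experimental ICUs | A: no program | B: program | C: program withdrawn |
| Control ICUs | D: no program | E: no program | F: program |

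The months follow from the period lengths 1, 5, 1, 5 and 1.

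**What each contrast estimates.** Let α be the arm difference (zero in expectation under randomization), π3 and π5 the background changes from P1 to P3 and to P5, δ the program effect at P3, γ the amount by which the program effect at P5 differs from δ, and κ any carry-over after withdrawal. Then:

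- B − E = α + δ
- B − C = π3 − π5 + δ − κ
- E − D = π3

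The coefficient of γ is zero in all three. A rank check agrees: the three contrasts have rank 3, and adding γ raises it to 4, so no combination of them yields γ. E − D contains only π3, which is season, secular trend and any reaction to being assessed, all under usual care.

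**What would carry γ.** Any such contrast must use F:

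- F − D = π5 + δ + γ
- (F − D) − (B − E) = γ + π5 − α

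P1 and P5 fall in the same calendar month, so π5 contains no season. It vanishes if there is no drift over 12 months. The expression can also be written (F − B) − (D − E), so the planned D versus E supplies the background-season correction, and F versus B is the missing part.

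**Precision of that estimate.** From the sample-size section: SD 14, ICC 0.1, 630 usable scores over 34 ICUs (630/34 = 18.53 per ICU-month), 17 ICUs per arm, and a target effect of 0.25 × 22 = 5.5 points. I assume that each assessment month yields this number, and that scores in one ICU in different periods share a cluster autocorrelation r, which the article does not give.

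- SE(F − D) = 14 × √[2 × (0.1 × (1 − r) + 0.9/18.53)/17]. At r = 0.8 this is 1.26.
- SE(B − E) = 14 × √[2 × (0.1 + 0.9/18.53)/17] = 1.85.
- With equal autocorrelation between all periods, the covariance of F − D with E cancels, so SE(difference) = √(1.26² + 1.85²) = 2.24.
- Detectable difference at 80% power and two-sided 5%: (1.96 + 0.84) × 2.24 ≈ 6.3 points.

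| r | SE(F − D) | SE(difference) | Detectable difference |
|---|---|---|---|
| 0 | 1.85 | 2.62 | 7.3 |
| 0.5 | 1.51 | 2.39 | 6.7 |
| 0.8 | 1.26 | 2.24 | 6.3 |
| 0.95 | 1.11 | 2.16 | 6.0 |

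Over this whole range the detectable difference exceeds 5.5 points.

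**The case against.** The strongest reply is that background seasonality was meant. The Abstract speaks of a seasonality effect without tying it to the program as closely as the Objectives section does. The only rationale in the Discussion is that case mix, and with it perceived discomfort, may vary over the year. Control ICUs at P1 and P3 supply the only repeated scores untouched by the program, so D versus E is a sensible place to look, and it is a useful companion to B versus C, which also spans six months. This stands in part: on that reading D versus E addresses a real question, and it is the Objectives and Design wording that is loose. It does not remove the conflict. Both sections refer to the program, the Design section's reason rests on a second program period that D versus E does not need, and the contrast still mixes season with six months of drift.

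Four stronger readings are tempting, and the article does not support them:

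- **That control P5 is never analysed.** This is a condensed article and a full analysis plan may exist. Only the contrasts named here can be judged.
- **That a third of the questionnaires are wasted.** This would count experimental P1, which the Design section collects as a baseline. The relevant cell is control P5, one of six.
- **That a promised confirmation is missing.** The Design section mentions confirmation in other ICUs as an eventual possibility. It is not a listed objective. The second period also serves sustainability and offers the program to every ICU.
- **That a season effect would be easy to detect.** The SE of 1.26 belongs to a simple before-after contrast. The program-by-season difference has an SE of about 2.24.

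The remedy has limits too. P5 has no concurrent untreated control, and P5 versus P1 is open to 12-month drift, just as D versus E is open to 6-month drift.

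**Conclusion.** The mismatch is established from the text alone and depends on no numerical assumption. The objective concerns seasonality of the program, while the contrast assigned to it has zero weight on the program in any season. It is not simply a detail left to an analysis plan, because the article names the arm, the periods and the cells.

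The consequence is limited to a secondary objective. It would lead to a mislabelled result, and it leaves the control P5 scores without a named use. The primary B versus E comparison does not change.

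A program-by-season estimate is possible from data already planned, but only as exploration. Its detectable difference of about 6.0 to 7.3 points is larger than the whole 5.5-point target, so a non-significant result would say little. Those figures rest on the sample-size inputs holding in every assessment month and on an assumed autocorrelation. Reading the estimate as program-by-season also requires no 12-month drift.

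**What to change.** 1. In the Data analysis section, label D versus E as seasonal or secular change under usual care.
2. Then choose one of two routes:
   - **Reword.** State the seasonality objective in the Objectives and Design sections as background variation in discomfort under usual care, and drop the argument that applying the program at another time of year is what makes it assessable.
   - **Add an exploratory analysis.** Fit one mixed model over the six arm-by-period cells, with random effects for ICU and for ICU-by-period. Estimate control P5 versus control P1 (months 13 and 1), set it beside B versus E, and report the difference with a confidence interval.
3. With the second route, state that P5 has no concurrent untreated control, that P5 versus P1 assumes no 12-month drift, and that the difference is not a confirmatory test.

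The cost is a change of wording and, on the second route, one extra model. No new data are needed, and the sample size and primary analysis stay as they are.
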